### Diagnostic criteria

2.5

Western medicine diagnostic criteria for UA were determined by referring to related guidelines for the management of NSTE-ACS.^[2,5,6]^ Traditional Chinese medicine (TCM) syndrome diagnostic criteria evaluation of UA is based on Standards for TCM industry of the People's Republic of China(ZY/T001.1–94).^[17]^ In the process of diagnosis and syndrome differentiation, 2 cardiac physicians of TCM will make the diagnosis respectively. If there exists diagnostic controversy, a consensus would be reached through further discussing or third-party advice.

### Eligibility criteria

2.6

Inclusion criteria:

Diagnosed with UA by a cardiac physician.18 to 80 years old.No gender restriction.Voluntary to participate and providing written informed consents, as required by Good Clinical Practice (GCP).

Exclusion criteria:

Angina pectoris caused by noncoronary stenosis such as abnormal thyroid function, cardiomyopathy, high adrenergic state, mental stress, left ventricular load increased (hypertension, aortic stenosis), tachycardia, violent activities, and so on.Patients with stroke or undergone PCI or coronary artery bypass grafting within 1 month before enrollment.Poorly controlled hypertension (systolic pressure ≥160 mm Hg or diastolic blood pressure ≥100 mm Hg).Patients with coexistent severe heart failure (New York heart association (NYHA), Class IV) and severe arrhythmia (atrial fibrillation, atrial flutter, paroxysmal ventricular tachycardia, sinus bradycardia [heart rate <55], complete left bundle branch block).Combined liver dysfunction (defined as Alanine transaminase (ALT) and/or Aspartate aminotransferase (AST) 3 times higher than the upper limit of normal) and kidney dysfunction (defined as creatinine clearance rate less than 30 mL/min/1.73 m^2^).The terminal phase cachexia of malignant tumors.High bleeding risk, such as hemorrhagic constitution, history of hemorrhage of vital organs (brain or upper gastrointestinal tract) within 6 months, low platelet counts, abnormal coagulation function, recent active hemorrhage, and so on.Underwent surgery within 1 month.Women who are under breastfeeding, pregnancy or preparing for pregnancy.Poor compliance.Known or suspected to be allergic to experimental drugs or allergic constitution.Patients who participate in any other clinical study or take any of its investigational drugs within the last 3 months.

### Termination and withdrawal criteria

2.7

All participants have right to withdraw from the trial depends on their own will. The reason will be recorded in the case report forms (CRFs) and the patient will continue standard western medicine treatment after withdrawing. The criteria of termination and withdrawal including:

The participant who has serious adverse events (AEs) may caused by experimental drug is considered to be inappropriate to continue the trial based on the cardiologist's judgment.The participant's condition becomes deteriorated or develops other diseases that may affect the study.Important deviations occur in the process of the clinical trial, such as poor compliance.The participant is not willing to continue the clinical trial.

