**Methods::**

A prospective, open-label, randomized, placebo-controlled clinical will be performed. A total of 60 patients diagnosed with UA will be randomly allocated to either the treatment group or the control group with a 1:1 ratio. The participants in the treatment group will receive LFN-G treatment and the participants in the control group will receive placebo. Meanwhile, both groups continue to undergo standard western medicine treatments. The duration of interventions is 4 weeks. The primary endpoint is the incidence of major cardiac adverse events, defined as a composite of recurrent angina, acute myocardial infarction (AMI), severe arrhythmia, heart failure, and cardiac death. Secondary outcomes include Seattle angina scale score, Chinese medicine syndromes and electrocardiograph (at weeks 0, 1, 2, 4), myocardial nuclides perfusion, measurement of wall motion score index and left ventricular ejection fraction, serum inflammation factors such as C-reactive protein, high sensitive-C-reactive protein, interleukin-6, matrix metalloproteinase-9, and so on (at weeks 0, 4). In addition, some biochemical indexes of blood and hematological indexes will be used to assess the safety of treatments. Any adverse effects of the treatment will be recorded.

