### Outcome measures

3.3

Primary outcome is the incidence of major cardiac adverse events, defined as a composite of recurrent angina, acute myocardial infarction, severe arrhythmia, heart failure, and cardiac death. This outcome will be compared with the baseline and the 4th week.

Secondary outcomes including:

(1)Seattle angina scale score: This score includes 4 aspects (physical activity limitation, angina frequency, treatment satisfaction, and disease cognition) and it can provide information of participants’ subjective assessment of therapy. This outcome will be compared the baseline with the 1st, 2nd, 3rd, and 4th week.(2)Chinese medicine syndromes: This outcome will be compared the baseline with the 1st, 2nd, 3rd, and 4th week.(3)ECG: The change of St-segment and T wave of baseline and the 1st, 2nd, 3rd, and 4th week.(4)Myocardial nuclides perfusion: It will be used to evaluate myocardial perfusion under endocardium and epicardium of the baseline and the 4th week.(5)Echocardiography: Measurement of wall motion score index and left ventricular ejection fraction of the baseline and the 4th week.(6)Vitro measurement: Measurement of serum inflammation factors such as C-reactive protein, high sensitive-C-reactive protein, interleukin-6, matrix metalloproteinase-9, and so on.

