### AEs

3.5

Any AEs will be requested to record in CRFs regardless of their relationship to the intervention. If serious AEs occur, the intervention should be stopped immediately and a detailed description of the time, severity, relationship with the drug, and the treatment measurement will be recorded. Serious AEs will be reported to the Steering Committee and Ethics Committee within 24 hours. In addition, a follow-up will be conducted until the AEs disappeared.

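### Section 2.7 does not separate stopping the granules from leaving the trial, which puts week-4 secondary measures at risk in patients who worsen; the primary composite is affected only marginally

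*Protocol article*

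**What the plan says.** Section 2.7 (Termination and withdrawal criteria) opens with the participant's right to leave the trial. It says that the reason is recorded and that standard western treatment continues. One undivided list of criteria follows:

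- a possibly drug-related serious adverse event, where the participant "is considered to be inappropriate to continue the trial based on the cardiologist's judgment";
- "The participant's condition becomes deteriorated or develops other diseases that may affect the study";
- "Important deviations occur in the process of the clinical trial, such as poor compliance";
- unwillingness to go on.

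Section 3.5 (AEs) uses narrower wording for one case: "If serious AEs occur, the intervention should be stopped immediately". It also provides that "Any AEs will be requested to record in CRFs regardless of their relationship to the intervention" and that "a follow-up will be conducted until the AEs disappeared".

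On timing, section 3.3 asks for "Measurement of wall motion score index and left ventricular ejection fraction of the baseline and the 4th week", and for perfusion at the same two points. The abstract gives the serum markers the same schedule: "interleukin-6, matrix metalloproteinase-9, and so on (at weeks 0, 4". Section 3.2 says that blood is drawn before and after the intervention. The Seattle score, the TCM syndrome and the ECG have intermediate visits. The primary outcome is a composite of recurrent angina, acute myocardial infarction, severe arrhythmia, heart failure and cardiac death, assessed at week 4. Section 2.4 states that neither participants nor investigators are masked.

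**The concern.** Stopping a study drug and ending a patient's follow-up are different decisions. Section 2.7 treats them as one. Deterioration, other disease and poor compliance are reasons to reconsider the granules. They are not reasons to stop measuring the patient, because getting worse is part of what the trial sets out to compare.

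If the list is applied as written, the patients who lack week-4 perfusion, echocardiography and serum values may be mainly those who did badly. These measures matter more than usual here: the Discussion relies on objective physical and chemical indicators for the reliability of the results, and an open-label trial needs them. The criteria leave room for judgement and are applied with the arm known, so the loss may differ between arms and bias the comparison in either direction. An SAP can set rules for missing values, but it cannot recover a scan or a sample that was never taken.

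**Working it through.** **1. No figure to reproduce.** The article gives 60 patients randomised 1:1, hence 30 per arm, and a two-sided 5% level. It gives no withdrawal rate, event risk, SD or power. Everything below is an illustration with 1 to 4 patients (3% to 13% of 30) withdrawn from one arm only and no true treatment effect.

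**2. Which data are exposed.**

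| Outcome | Scheduled | Effect of withdrawal in between |
|---|---|---|
| Perfusion, echocardiography | weeks 0 and 4 | possibly no post-baseline value |
| Serum markers | weeks 0 and 4 | a sample at stopping is possible under section 3.2, but it is not a week-4 value |
| Seattle score, TCM syndrome, ECG | also at intermediate visits | only later visits are lost |
| Primary composite | to week 4 | lost only if no component was recorded first and an event follows |

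**3. Secondary measures, upper bound.** Suppose the k withdrawn patients are exactly the k worst of 30 on a normally distributed measure. The expected four largest order statistics of 30 standard normals are 2.043, 1.616, 1.365 and 1.179. The mean of those left shifts by (sum of the top k)/(30 − k):

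- k = 1: 2.043/29 = 0.070 SD
- k = 2: 3.659/28 = 0.131 SD
- k = 3: 5.024/27 = 0.186 SD
- k = 4: 6.203/26 = 0.239 SD

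**4. Secondary measures, partial dependence.** If withdrawal is driven by a severity that correlates 0.5 with the measure, each shift is multiplied by 0.5: 0.035, 0.065, 0.093 and 0.119 SD. If withdrawal is unrelated to the measure, the shift is 0.

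**5. Scale.** A two-sample t test with 30 per arm, two-sided 5%, has 80% power for a difference of 0.736 SD. The upper bound is therefore 10% to 32% of that difference (0.070/0.736 to 0.239/0.736). The correlation-0.5 case is 5% to 16% (0.035/0.736 to 0.119/0.736). Under the no-effect assumption, equal loss of the same kind in both arms shifts both means alike and leaves no bias, only less information.

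**6. Primary outcome: why no range is given.** Let p be the overall 4-week risk, w the number withdrawn without a component, and r their risk of an event between withdrawal and week 4. Counting them event-free lowers the observed rate by w·r/30. Excluding them gives (30p − w·r)/(30 − w). The residual risk r can lie on either side of p:

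- *Below p.* An event-free patient is at risk only for the remaining days. With a constant hazard and withdrawal at day 14 of 28, r = 1 − √(1 − p): 10.6% for p = 20% and 16.3% for p = 30%.
- *Above p.* If withdrawal marks a sicker patient, r may be higher; take 60% as an example.

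With p = 30% and w = 4, exclusion gives (9 − 0.65)/26 = 32.1% for r = 16.3%, which is 2.1 points too high. For r = 60% it gives (9 − 2.4)/26 = 25.4%, which is 4.6 points too low. The sign depends on an r that the article does not give.

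**The case against.** The strongest objection is that this argues from silence in a condensed article. Section 2.7 nowhere says that visits or imaging cease. Its opening sentence on leaving the trial is about voluntary withdrawal, where ending follow-up can be legitimate. The deterioration and compliance items do not say what is being stopped. A separate ethics-approved protocol exists and might provide for continued assessment.

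That limits how firmly the point can be put, but does not remove it. The article does not merely leave a procedure out: it states the criteria, places worsening and poor compliance in the same list as unwillingness to continue, and frames the list as withdrawal. Section 3.5 shows that the narrower wording was available. It is used there for serious adverse events only, and the follow-up it adds runs until the event resolves, not to week 4.

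Three stronger readings are tempting and are not supported:

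- *That withdrawal on worsening is compulsory.* The list is not worded as mandatory, and the qualifier about affecting the study may apply to deterioration as well as to other disease.
- *That patients who have a primary event drop out of the primary analysis.* Adverse events are recorded whatever their cause, so a component that occurs before withdrawal should be on record, and later events cannot change a binary composite. The composite includes recurrent angina, so in this population much cardiac worsening would already count.
- *That the primary result is biased by a stated number of points in a known direction.* Step 6 of the working shows that exclusion can push the rate either way.

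It is also fair to say that the secondary shifts are modest, and that placing every withdrawal in one arm is an unfavourable assumption.

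**Conclusion.** The point holds for the week-4 secondary measures, chiefly perfusion, echocardiography and serum markers. As worded, section 2.7 allows them to be lost selectively in patients who worsened and possibly unequally by arm. With 30 per arm and 1 to 4 patients withdrawn from one arm only, the illustrated shift is 0 SD if withdrawal is unrelated to the measure, 0.04 to 0.12 SD at a correlation of 0.5, and 0.07 to 0.24 SD as an upper bound. The number withdrawn, the one-sided loss and the correlation are assumptions, not figures from the article.

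For the primary composite the exposure is marginal: patients withdrawn without a recorded component who then have an event before week 4. Neither its size nor its direction can be derived.

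This is a cheap improvement of minor to moderate severity. Confidence is medium, because the full protocol is not shown and might already keep such patients in follow-up.

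**What to change.** Reword section 2.7 on the model of section 3.5. Deterioration, other disease, poor compliance or a drug-related serious adverse event may stop the granules but not follow-up; only withdrawal of consent ends follow-up. Ascertain MACE to week 4 by call or visit in every randomised participant. Obtain the week-4 measures already scheduled (perfusion, echocardiography, serum, ECG, Seattle score) where feasible.

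The cost is a change of wording, a CRF field that distinguishes granules stopped from consent withdrawn, and a few extra calls or attendances. No new test is needed. Some patients will be too unwell or unwilling to attend, so some week-4 secondary data will still be missing.

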### Test drugs

2.8

Drugs for clinical trials are LFN-G and placebo (LFN-G mimics), provided by the Guangdong E-Fong Pharmaceutical Technology Development Co, Ltd (Guangdong, China). Formula ingredients of LFN-G includes: Lumbricus (Di long) 10 g, Radix Clematidis (Wei lingxian) 15 g, Radix Cynanchi Paniculati (Xu changqing) 12 g, Panax notoginseng (San qi) 3 g, Astragalus (Huang qi) 10 g, and Borneol (Bing pian) 0.1 g. All ingredients are herbal granules. These granules are mixed and packaged into 2 single-dose sachets, each weighing 25.05 g. The placebo consists of medical starch dextrin without active ingredients. Through adding a variety of food colorings and flavouring agents, the placebo will present a similar weight, appearance and taste as close as possible to the real LFN-G.

## Treatment

3

### Treatment plan

3.1

All participants will receive a standard western medicine treatment in accordance with guidelines^[2,5,6]^ judged by a senior cardiology physician, including but not limited to anti-myocardial ischemia therapy, antiplatelet or anticoagulation therapy, statin therapy. Meanwhile, all participants will accept lifestyle adjustments.

Experimental group: Participants will receive LFN-Gs (divided into 2 equally- weight in separate packages, each 25.05 g), dissolving each package in 100 mL warm boiled water after breakfast and supper for 4 weeks.

Control group: Patients will be given placebo granules (divided into 2 equally- weight in separate packages, each 25.05 g). The administration is in accordance with the experimental group.

### Collection of serum

3.2

The subject blood samples will be collected by a designated nurse before and after intervention and designated investigator will centrifuge blood samples in the laboratory. After centrifugation, the supernatant was transferred in frozen pipe and stored at −80°C for preservation in the biological sample bank of the Dongzhimen hospital. All samples will be destructed when the trial end.

### Outcome measures

3.3

Primary outcome is the incidence of major cardiac adverse events, defined as a composite of recurrent angina, acute myocardial infarction, severe arrhythmia, heart failure, and cardiac death. This outcome will be compared with the baseline and the 4th week.

Secondary outcomes including:

(1)Seattle angina scale score: This score includes 4 aspects (physical activity limitation, angina frequency, treatment satisfaction, and disease cognition) and it can provide information of participants’ subjective assessment of therapy. This outcome will be compared the baseline with the 1st, 2nd, 3rd, and 4th week.(2)Chinese medicine syndromes: This outcome will be compared the baseline with the 1st, 2nd, 3rd, and 4th week.(3)ECG: The change of St-segment and T wave of baseline and the 1st, 2nd, 3rd, and 4th week.(4)Myocardial nuclides perfusion: It will be used to evaluate myocardial perfusion under endocardium and epicardium of the baseline and the 4th week.(5)Echocardiography: Measurement of wall motion score index and left ventricular ejection fraction of the baseline and the 4th week.(6)Vitro measurement: Measurement of serum inflammation factors such as C-reactive protein, high sensitive-C-reactive protein, interleukin-6, matrix metalloproteinase-9, and so on.

### Safety assessment

3.4

The dosage of experimental herbs used in this trial is all within the recommended range based on the People's Republic of China Pharmacopeia (2015 edition). At the process of trial, we also utilize laboratory tests to evaluate liver and kidney function to ensure the safety of participants from the time of enrollment through the follow-up period.

### AEs

3.5

Any AEs will be requested to record in CRFs regardless of their relationship to the intervention. If serious AEs occur, the intervention should be stopped immediately and a detailed description of the time, severity, relationship with the drug, and the treatment measurement will be recorded. Serious AEs will be reported to the Steering Committee and Ethics Committee within 24 hours. In addition, a follow-up will be conducted until the AEs disappeared.

### Data management and quality control

3.6

All information related with this trial will be recorded in CRFs by a trained and qualified investigator. No correction of completed CRFs is allowed once completed. The record of CRFs will be reviewed by the clinical inspector. To ensure the accuracy of the data, 2 investigators will input and proofread the data respectively. In addition, all papery documents and electronic versions of the CRF will be preserved in the secure research archives for 5 years after trial completing at the Dongzhimen Hospital Affiliated to Beijing University of Chinese Medicine and only can be viewed by the research team.

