### Randomization and masking

2.4

A designated investigator of our team will use an interactive Web response system to randomly allocate participants to receive either LFN-G or placebo after enrollment in a 1:1 ratio. Randomization will be stratified by age, sex, morbid status, and comorbidities. Due to this trial is an open-label trial, so neither participants nor investigators is not masked to the treatment option.

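### Section 3.6 bars any correction of a completed CRF, so an error found on review would, as written, pass into the analysed data

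*Protocol article*

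**What the plan says.** Section 3.6 of the protocol article (Data management and quality control) makes four statements that bear on this point, in this order:

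- Scope: "All information related with this trial will be recorded in CRFs by a trained and qualified investigator".
- Correction: "No correction of completed CRFs is allowed once completed".
- Review: "The record of CRFs will be reviewed by the clinical inspector".
- Entry: "To ensure the accuracy of the data, 2 investigators will input and proofread the data respectively".

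Section 3.5 (AEs) puts adverse events on the same forms: "Any AEs will be requested to record in CRFs regardless of their relationship to the intervention". Section 2.7 (Termination and withdrawal criteria) does the same for reasons for withdrawal. Section 2.4 (Randomization and masking) makes the trial open-label, so the people who complete the CRFs know the allocation.

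The ban takes effect when a form is completed, not at database lock. The article does not define completion, does not say when the inspector reviews, and attaches no exception to the ban.

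**The concern.** A CRF can be wrong against its source: a misdated event, a score item in the wrong box, a laboratory value in the wrong unit. Review exists to find such entries and have them put right while keeping a record of the change. A flat ban on correction removes the second step. The error is then either analysed although someone knows about it, or dealt with in some way that the stated rule does not cover.

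The CRF carries all trial information, so the primary composite, the secondary outcomes and the safety data all depend on it. The trial is also open-label. When those recording the data know the allocation, a traceable correction against source is one of the few ways to show later why a value is what it is. Silent overwriting would be a real hazard in that setting, and a ban may be meant to prevent it. The usual protection, however, is to keep the old entry visible beside the new one, not to forbid the new one.

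**Working it through.** No arithmetic applies. The question is whether the rules of section 3.6 can all be followed and still serve the aim that the section sets itself. To test this, follow one wrong entry through them.

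1. **Recording.** An investigator enters a value that differs from the source, and the form is completed. By the scope statement, any item of trial data can be affected.
2. **Ban.** From this moment the form may not be corrected. No section of the article gives an exception or an amendment route.
3. **Review.** The inspector reads the form and notices the discrepancy. The review has worked as detection. Because of step 2, the finding cannot lead to a corrected form.
4. **Entry.** Two investigators enter and proofread. As described, this checks what goes into the database. Nothing in the description compares the CRF with the source. Both people can copy the wrong value correctly, their entries agree, and the check passes.
5. **Analysis.** The wrong value reaches the analysed data even though it was detected at step 3.

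Two comparisons follow.

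- **Ban against review.** Both can be carried out, but for completed forms the ban removes the review's ability to correct.
- **Ban against the accuracy aim.** The aim introduces the entry step, which protects against entry errors only. For errors on the CRF itself, correction after review is the remedy the section would need, and it is the one thing ruled out.

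**Size.** An expected number of uncorrected errors would need the number of values recorded, the rate of CRF errors against source, and the share of those errors that the inspector detects. The article gives neither an error rate nor a detection share. Any count would be driven by the assumed rates, so none is offered.

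**The case against.** The strongest reply has three parts.

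**The article is condensed.** Section 2.1 refers to a final protocol that is not shown. Query handling, audit trail and database lock commonly sit in such a document or in a data-management plan, so their absence here is no fault. That is right, and the point does not rest on their absence. It rests on a sentence that the article does state. A fuller document that allowed corrections would contradict that sentence.

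**The wording may be loose.** The article's English is imprecise elsewhere, as in section 2.4: "Due to this trial is an open-label trial, so neither participants nor investigators is not masked to the treatment option". The authors may have meant only that existing entries must not be overwritten, or that forms are closed after the inspector has signed them off. Either reading is plausible, and the second would reconcile ban and review. The text says neither. This is a good reason to ask for rewording rather than to assume that the site will work to the literal rule.

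**Stronger readings go too far.** Three are tempting, and the objection to each stands.

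- A reader might infer that the inspector's review serves no purpose. It can still detect deviations, poor compliance, unreported events and missing forms. Only its corrective function is lost.
- A reader might infer a conflict with section 3.5, because "a follow-up will be conducted until the AEs disappeared". That section does not say that causality is re-assessed, nor that an AE form counts as completed while the event is open. Adding an outcome to an open form need not be a correction at all.
- A reader might infer that primary events are few, so that one or two wrong entries would decide the trial. The article gives no event rate, and the composite in section 3.3 includes recurrent angina in patients enrolled with unstable angina. Events need not be few.

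**Conclusion.** The point holds as a defect in one stated rule. Section 3.6 forbids correction of completed CRFs without exception. Followed literally, this lets a detected CRF error pass into the analysis, defeats the corrective purpose of the inspector's review and works against the section's aim of accurate data.

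The conclusion rests on two readings of the text: that completion can precede the inspector's review, which the article leaves open, and that two-person entry checks transcription only, which is how it is described.

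No effect on the estimate, the type I error or the trial's conclusion has been shown, and none can be calculated from the documents. The case for acting is that the rule is wrong as written and almost free to put right.

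**What to change.** Replace the sentence in section 3.6 with a rule along these lines:

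- Entries on a CRF may not be erased or overwritten.
- Until database lock, an entry may be corrected against the source document, including after a query from the clinical inspector. The original entry stays legible, and the new value, the reason, the date and the role of the person making the change are recorded.
- After lock, no change is made without a documented unlock.

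The same rule should cover the electronic version of the CRF that section 3.6 mentions. If a fuller data-management document already provides for this, it is enough to bring the sentence in section 3.6 into line with it.

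The cost is one paragraph of text, a simple query form and a small amount of data-management time. Sample size, treatment and endpoints are untouched.
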